### Ethical Considerations

This study adheres to the ethical principles set out in the Declaration of Helsinki and the Malaysian Good Clinical Practice Guidelines. Ethical approval has been granted by the IIUM Research Ethics Committee (IREC-2026‐582) prior to the commencement of any recruitment activities. Any protocol deviation will be reported to the IIUM Research Ethics Committee. The study’s procedures, risks, and benefits are clearly explained by the principal investigator to both the patient and parent or guardian, and they are encouraged to ask questions. They also received a patient information sheet to take home and review before deciding whether to participate. Those who agreed to participate are required to sign the appropriate forms: participants younger than 18 years complete an assent form, and their parent or legal guardian signs the informed consent form, whereas participants older than 18 years sign the informed consent form. Participation in the study is entirely voluntary. No payments will be given for participation, and there are no costs involved in joining the study. All personal data are kept confidential in a password-protected laptop, and no participant’s identifiable data are mentioned in publications or presentations. Permission will be obtained from the Director General of Health before any planned publication and presentation of trial results.

### Sample Size Calculation

The sample size is determined using G*Power (Version 3.1.9.6, Heinrich Heine University, Düsseldorf, Germany). To assess the effect of laceback on a patient’s oral hygiene, a previous split-mouth study using the Orthodontic Plaque Index (OPI) to record plaque score on orthodontic patients will be used in this study [23]. By referring to the SEM and sample size (n) reported in that study, the SD of OPI is calculated to be 1.88 by applying the formula $SD=SEM\times \sqrt{n}$. A difference of 1 point in OPI was deemed clinically meaningful to be detected. A total of 34 participants are needed for 68 sites (34 laceback and 34 no laceback), which would give a power of 85% with a significance level of 0.05 to detect a 1-unit difference in OPI score. Assuming a 10% dropout rate, 38 participants are recruited, providing a total of 76 sites (38 laceback and 38 no laceback).

### Study Conduct

#### Randomization: Sequence Generation, Allocation Concealment, Implementation

Placement of laceback ligatures is randomly allocated to the participants’ left or right side. This study intends to balance 5 prespecified covariates between the laceback and no laceback groups:

Upper first premolar extractionUpper second premolar extractionLower first premolar extractionLower second premolar extractionSide of allocation (number of participants receiving laceback on the left vs right side)

The method of randomization used is the minimization method (also known as “covariate adaptive randomization”) [24]. This is because minimization achieves a better balance than stratified randomization when sample sizes are small (<100 participants) and several prognostic factors (≥3) need to be controlled simultaneously [25]. Therefore, this study uses a 2-stage randomization strategy: simple randomization, followed by minimization.

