## Methods

### Study Design

This is a single-center, single-blind, split-mouth randomized controlled trial with a 1:1 allocation ratio for the 2 groups (left and right sides of the oral cavity). In this study, either the left or right side of each participant’s oral cavity is randomly assigned to receive a laceback, while the contralateral side serves as the control (no laceback). The study is aimed to fulfill as many items as possible in the CONSORT (Consolidated Standards of Reporting Trials) 2025 checklist for reporting randomized controlled trials, and the SPIRIT (Standard Protocol Items: Recommendations for Interventional Trials) 2025 checklist for preparing protocols of randomized controlled trials [18,19].

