#### Simple Randomization

For the first 10 participants, simple randomization is applied to ensure an equal number of participants receive laceback intervention allocated to the left side (n=5) and to the right side (n=5) [26]. The random sequence is generated by an independent coinvestigator not directly involved in participant recruitment, using computer-generated random numbers in Microsoft Excel (2023). Allocation concealment is maintained using sequentially numbered, opaque, sealed envelopes containing the allocation card written “left” or “right.” These are kept secure in a separate box to prevent foreknowledge by the treating clinician and principal investigator. Whenever a new participant is recruited, an independent dental nurse is tasked to open the subsequent envelope to reveal the side allocated for laceback ligature. The cumulative counts of each covariate on the laceback and no laceback group for the first 10 participants are recorded.

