#### Minimization

For the remaining 28 participants, allocation is determined using the minimization method. First, each participant’s finalized extraction pattern (left and right, upper and lower premolar type) is recorded. Overall, 2 hypothetical allocations are then evaluated: laceback on the left or laceback on the right. For each option, an imbalance score is calculated as the sum of absolute differences between the 2 trial arms across the 5 covariates, based on the cumulative allocations of all previously enrolled participants. The option with the lower imbalance score is considered the favored allocation [24,27].

The next step involves performing a biased-coin draw, whereby the favored side is allocated with a probability of *P*=.8, and the other side with a probability of *P*=.20 [28,29]. The purpose of introducing this random element is to reduce the predictability of the next assignment while intentionally biasing the allocation toward the arm with a lower imbalance score [27,30]. To achieve this, a fully opaque container holds 10 identical slips: 8 “favored” slips and 2 “other” slips. If the research assistant draws a “favored” slip, the minimization-favored allocation is selected (ie, the option with lower imbalance score). If an “other” slip is drawn, the opposite allocation is applied (ie, the option with the higher imbalance score). In the event that the imbalance scores for left and right are identical, a 50:50 draw (5 “left” and 5 “right” slips) will be performed instead. All allocations are documented in an allocation log, including the participant’s extraction pattern, preallocation cumulative covariate totals, imbalance scores for both options, slips drawn, and final assignment. Allocation concealment is preserved until the moment of assignment. The randomization protocol is illustrated in Figure 1.

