### Intended Statistical Analysis

Statistical analysis is conducted using IBM SPSS Statistics (version 31). Descriptive statistics are used to report participant demographics, baseline characteristics, and frequency of laceback complications. To assess whether the data are normally distributed, interpreting the shape of the histogram and the Shapiro-Wilk test are used. Intra- and interrater reliability for plaque score assessment are measured using Cohen kappa. The threshold for good inter- and intrarater reliability is set to be more than 0.8.

Repeated outcome measurements of plaque scores will be analyzed using a mixed model for repeated measures. The model includes treatment group, time, and treatment-by-time interaction as fixed effects, with participant included as a random effect. A mixed model for repeated measures allows inclusion of participants with incomplete follow-up data without requiring formal imputation, assuming data are missing at random. If the data are not normally distributed, plaque scores over time (T_0_, T_1_, and T_2_) will be compared using the Friedman test.

From the pain diary gathered, the pain scores are plotted against time to allow calculation of area under the curve (AUC) using the trapezoidal rule [34]. Pain AUC will be calculated between T_0_ and T_1_ and T_1_ and T_2_. The mean pain AUC for laceback and no laceback sides will be calculated by averaging pain AUC values between T_0_ and T_1_ and between T_1_ and T_2_. To compare differences in mean pain AUC of laceback and no laceback groups, a paired *t* test is used if data are normally distributed. If the normality assumption is violated, the Wilcoxon signed-rank test is applied instead.

The mean frequency of archwire complications is recorded by summing up the number of complications that happen throughout the study period from T_0_ to T_2_. To compare differences in the mean frequency of archwire complications between the laceback and no laceback groups, a paired *t* test is used if data are normally distributed. The mean frequency of laceback complications and the number and percentage of participants with at least 2 laceback complications are also reported. The value of *P*<.05 is considered statistically significant.

Sensitivity analysis will be conducted by comparing the results of intention-to-treat and per-protocol analyses. If both analyses yield similar results, this demonstrates the robustness and validity of the study’s conclusions.

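### Allocation is balanced on the side receiving the laceback, but the primary plaque model has no left/right term, so any systematic left-right difference stays in the residual and enlarges the standard error

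*Protocol article*

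**What the plan says.** In the Protocol article, the section Randomization: Sequence Generation, Allocation Concealment, Implementation states: "This study intends to balance 5 prespecified covariates between the laceback and no laceback groups". Four of these covariates concern which premolar was extracted (upper or lower, first or second). The fifth is side of allocation, defined as the "number of participants receiving laceback on the left vs right side".

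Balance on side is actively enforced. The section Simple Randomization fixes a 5/5 split: "For the first 10 participants, simple randomization is applied to ensure an equal number of participants receive laceback intervention". The section Minimization continues: "For the remaining 28 participants, allocation is determined using the minimization method", with a biased coin of 0.8 towards the option with the lower imbalance score.

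The section Intended Statistical Analysis lists the terms of the plaque model: "The model includes treatment group, time, and treatment-by-time interaction as fixed effects, with participant included as a random effect". Neither side of mouth nor premolar type is among them. The paired tests for pain AUC and archwire complications are also described without reference to side.

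**The concern.** In a split-mouth trial, side of mouth plays the part that period plays in a two-period crossover. It is a nuisance factor crossed with treatment within each participant. Balancing it protects the estimate. The precision that this balance offers reaches the confidence interval only if the factor is also in the model.

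If it is left out, and left and right differ on average, the interval is wider than it would be with side included. A real plaque difference is then somewhat less likely to be detected. The participant random effect does not help, because it captures only what the two sides of a mouth share.

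**Working it through.** **Inputs from the article.** 34 evaluable participants, 38 recruited, a difference of 1 OPI point, SD 1.88, power 85%, alpha 0.05 (Sample Size Calculation); visits T0, T1 and T2 (Primary Outcome: Plaque Score); the allocation rules and model terms above.

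**Inputs assumed.** The systematic left-minus-right OPI difference d, taken from 0 to 0.5, and paired-difference SDs s of 0.5 to 0.8 besides the planning value. The article gives neither d nor an SD below 1.88.

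**1. The plan's own figure.** A two-sided paired t test with standardised effect 1/1.88 = 0.532 needs n = 34 (power 0.853; n = 33 gives 0.842). With 10% dropout, 34/0.9 = 37.8, so 38. The stated numbers reproduce, with 1.88 acting as the SD of the paired difference.

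**2. What balance does to the estimate.** The laceback-minus-control difference is τ + d when the laceback is on the left and τ − d when it is on the right. The mean difference is therefore off by d × (L − R)/n. Simulating the documented allocation (5/5, then 28 by the 0.8 coin, symmetric extractions) gives an SD of L − R of about 1.1, against 6.2 for coin tossing. With d = 0.3 and n = 38, the residual disturbance has SD 0.3 × 1.1/38 = 0.009 OPI points. The shift is almost gone from the estimate.

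**3. What omission does to the SE, single-visit contrast.** The paired differences have variance s² + d² without side and s² with it:

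SE ratio = √(1 + d²/s²).

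**4. The same in the stated three-visit model.** Assume for now that no participant-by-side variance persists across visits. The shift puts ±d/2 in each of six cells per participant, a sum of squares of 6 × d²/4 = 1.5d². Residual degrees of freedom are 6n − n − 5 = 5n − 5, about 5 per participant, so the residual variance rises by about 0.3d². Without the shift it is s²/2. Hence

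SE ratio = √(1 + 0.6d²/s²).

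| d | s | Single visit | Three-visit model |
|---|---|---|---|
| 0 | any | 1.000 | 1.000 |
| 0.2 | 0.6 / 0.8 | 1.054 / 1.031 | 1.033 / 1.019 |
| 0.3 | 0.6 / 0.8 | 1.118 / 1.068 | 1.072 / 1.041 |
| 0.5 | 0.6 / 0.8 | 1.302 / 1.179 | 1.190 / 1.111 |
| 0.2 | 1.88 | 1.006 | 1.003 |
| 0.3 | 1.88 | 1.013 | 1.008 |
| 0.5 | 1.88 | 1.035 | 1.021 |

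At s = 1.88, power for the single-visit contrast with n = 34 falls from 0.853 to 0.849, 0.844 and 0.829 for d = 0.2, 0.3 and 0.5.

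**5. Check by simulation.** For the T2-minus-T0 contrast with n = 38 and s = 0.5, the simulated SE ratios are 1.05, 1.10 and 1.27 for d = 0.2, 0.3 and 0.5. The formula in step 4 gives 1.047, 1.103 and 1.265. Type I error is 0.036, 0.028 and 0.012 without side, and about 0.05 with it.

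**6. Relaxing the assumption in step 4.** Let 30% of the paired-difference variance (s = 0.5) be a participant-specific side difference that persists over visits. Omitting side still enlarges the SE of the T2-minus-T0 contrast, with ratios of 1.06, 1.12 and 1.31. The reported SE is then no longer correct with or without the side term. For an all-visit contrast at d = 0, type I error is about 0.14 either way, and about 0.25 when the persistent share is 60%.

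**The case against.** **No left-right difference is documented.** The article reports none and does not mention handedness. Balancing on side shows a wish for equal numbers; it does not show that the investigators expect plaque to differ by side. This stands, and so the size can only be given as a range that includes zero.

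**At the plan's own SD the loss is small.** This also stands: at most about 3.5% of the SE for d up to 0.5. In reply, the side score is an average bounded by 0 and 4, for which the largest possible SD is 2. A paired-difference SD below 1.88 is therefore plausible, but the article supplies no such value.

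**The unseen analysis plan may include side.** The section Clinical Trial Registration says that an intended analysis plan is held at the registry. However, the article itself enumerates the fixed effects, so this is a stated model and not a detail left open.

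A reader might also infer stronger points, which the documents do not support:

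- *That the SE is too large and the test conservative in all circumstances.* The model also has no participant-by-side term, and step 6 shows that the SE can then be too small for some contrasts. What holds is the comparison: where d is not zero, the SE without side exceeds the SE with side.
- *That the single-visit 7 to 12% applies to the primary analysis.* The stated model uses three visits, and the corresponding figure is about 4 to 7%.
- *That all five allocation factors must be in the model.* Eligibility requires bilateral extractions. With a symmetric pattern, premolar type is the same on both sides and cancels within the mouth. It matters only for asymmetric patterns, whose frequency is not given.
- *That planned power is lost.* The sample size calculation claims no gain from minimisation or from adjusting for side.
- *That pain and archwire results suffer to a known degree.* The paired tests share the structure, but nothing in the article supports a left-right difference of any particular size for them.

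**Conclusion.** The point holds as a modest matter of efficiency. The trial controls the side allocated to the laceback by design and then leaves side out of its stated plaque model. Any systematic left-right plaque difference stays in the residual and widens the interval relative to a model with side; it causes no material bias.

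The size depends on d and s, and d is not in the documents. It is nil at d = 0. At d = 0.3 with s of 0.6 to 0.8 it is about 4 to 7% of the SE in the three-visit model, equivalent to 8 to 13% of the information (1 − 1/1.084 to 1 − 1/1.15). At s = 1.88 and d up to 0.5 it is at most about 3.5% for a single visit, and about 2% in the three-visit model. The three-visit percentages assume no persistent participant-by-side variance. The change is worth making because it is almost free, even if the gain proves small.

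**What to change.** Add side of mouth (left/right) as a fixed effect in the primary plaque model. In the paired comparisons of pain AUC and archwire complications, adjust for the side allocated to the laceback, as in a two-sequence crossover analysis. Terms for premolar type are optional and useful only if a meaningful number of participants have asymmetric extraction patterns. If the registered analysis plan already includes side, bring the article's text into line with it.

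The cost is about one degree of freedom and a sentence of text. The section Minimization says that the final assignment and extraction pattern are already in the allocation log. The analyst can be given the left/right label with a masked arm code, so blinding is not affected. With the primary analysis scheduled for completion by October 2027, the term can still be specified before codes are released.

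The side term does not by itself make the SE correct if participant-by-side variance persists over visits. The covariance structure for the two sides of a mouth is a separate point and should be settled alongside this one.

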#### Simple Randomization

For the first 10 participants, simple randomization is applied to ensure an equal number of participants receive laceback intervention allocated to the left side (n=5) and to the right side (n=5) [26]. The random sequence is generated by an independent coinvestigator not directly involved in participant recruitment, using computer-generated random numbers in Microsoft Excel (2023). Allocation concealment is maintained using sequentially numbered, opaque, sealed envelopes containing the allocation card written “left” or “right.” These are kept secure in a separate box to prevent foreknowledge by the treating clinician and principal investigator. Whenever a new participant is recruited, an independent dental nurse is tasked to open the subsequent envelope to reveal the side allocated for laceback ligature. The cumulative counts of each covariate on the laceback and no laceback group for the first 10 participants are recorded.

#### Minimization

For the remaining 28 participants, allocation is determined using the minimization method. First, each participant’s finalized extraction pattern (left and right, upper and lower premolar type) is recorded. Overall, 2 hypothetical allocations are then evaluated: laceback on the left or laceback on the right. For each option, an imbalance score is calculated as the sum of absolute differences between the 2 trial arms across the 5 covariates, based on the cumulative allocations of all previously enrolled participants. The option with the lower imbalance score is considered the favored allocation [24,27].

The next step involves performing a biased-coin draw, whereby the favored side is allocated with a probability of *P*=.8, and the other side with a probability of *P*=.20 [28,29]. The purpose of introducing this random element is to reduce the predictability of the next assignment while intentionally biasing the allocation toward the arm with a lower imbalance score [27,30]. To achieve this, a fully opaque container holds 10 identical slips: 8 “favored” slips and 2 “other” slips. If the research assistant draws a “favored” slip, the minimization-favored allocation is selected (ie, the option with lower imbalance score). If an “other” slip is drawn, the opposite allocation is applied (ie, the option with the higher imbalance score). In the event that the imbalance scores for left and right are identical, a 50:50 draw (5 “left” and 5 “right” slips) will be performed instead. All allocations are documented in an allocation log, including the participant’s extraction pattern, preallocation cumulative covariate totals, imbalance scores for both options, slips drawn, and final assignment. Allocation concealment is preserved until the moment of assignment. The randomization protocol is illustrated in Figure 1.

**Figure 1. F1:**
[figure not shown]
Randomization protocol. SNOSE: Sequentially numbered, opaque, sealed envelopes.

### Intervention

On one side that is randomly allocated, passive laceback is placed on the maxillary and mandibular arches prior to ligating the archwires. This is termed as “laceback side.” Laceback is not placed during the bond-up appointment, but 1 week after that (T_0_). Data collection for pain also commences after T_0_. This is to minimize the confounding effect of pain arising from initial archwire placement, which tends to subside in 1 week, as reported in the literature [31].

#### Standardization of Laceback Placement

Laceback is placed by the principal investigator using a preformed 0.010-inch stainless steel wire ligature (Ormco Corp). A trial on a study model fitted with Master Series, 0.022-inch slot, MBT prescription metal brackets (American Orthodontics) on the buccal segment was conducted to determine and standardize the method of securing a passive laceback.

First, the loop of the preformed long ligature was placed over the first molar hook. The ligature wire was then tied passively in a figure-of-eight pattern from the hook of the first permanent molar tube to the canine bracket of the same quadrant. At this stage, the ligature wires were not kept loose, but just taut enough as they passed above and below each bracket. Next, the free ends of the ligature wire were held together using Mathieu pliers at 5 mm from the mesial edge of the canine bracket. During the standardization process, it was determined that 5 twists of the ligature wire were required to position the knot just adjacent to the mesial wing of the canine bracket. This technique ensured that the laceback remained passive and was not overtightened, as shown in Figure 2. In addition, when lacebacks were placed on the participants, the gingiva surrounding the canine, premolar, and molar teeth was inspected to ensure that no blanching occurred, as this would indicate overtightening—a condition that this study aims to avoid. Finally, the excess wire was cut off using ligature cutters, leaving 3 mm of twisted wire (pigtail), which was tucked gingivally behind the canine bracket using a ligature tucker.

**Figure 2. F2:**

Trial on a study model to standardize the method of securing passive laceback.

#### Interventions Common to Both Groups

The participants of this research undergo active orthodontic treatment at the postgraduate orthodontic clinic. The same bracket system, Master Series, 0.022-inch slot, MBT prescription metal brackets (American Orthodontics), and initial archwire (0.014-inch Euroform Super Elastic Nickel Titanium; Ortho-Care) are used for all participants. All brackets are bonded using the same standardized protocol, which involves 37% phosphoric acid etchant (Acid Etchant; American Orthodontics), light-cured adhesive primer (reliaBond Light-Cure Bonding Adhesive 5th Generation; Advanced Healthcare Ltd), and orthodontic composite resin (BracePaste Adhesive; American Orthodontics), following the manufacturer’s instructions. Extractions of all first or second premolars are done at least 2 weeks before the appointment for bond-up of orthodontic fixed appliances, so as to minimize pain arising from the extraction site that may confound the pain assessment. Archwires are ligated using elastomeric modules (EKSEN). The ends of the archwires are cut flush to the molar tubes and not cinched. Bite planes, intermaxillary elastics, headgear, or any auxiliaries are not used during the study period. The principal investigator delivers oral hygiene instructions, dietary instructions, and braces care instructions verbally with demonstration on a model using a standard script. An educational video on post-bond-up instructions is created and sent to the participants’ mobile devices for viewing. A patient information leaflet on brace care is also provided. All participants are supplied with a fluoridated toothpaste (Colgate Maximum Cavity Protection Fresh Cool Mint Toothpaste; Colgate-Palmolive Company) and a soft-bristle toothbrush (Colgate Zig Zag Toothbrush; Colgate-Palmolive Company). They are requested not to use any additional oral hygiene aids throughout the duration of the research. Participants undergo one round of scaling before lacebacks are placed during T_0_. Thereafter, they are informed not to go for professional teeth cleaning during the study period. Participants are reminded to check their braces for any dislodgement and breakage twice daily (morning and evening). If there are any orthodontic emergencies, participants are advised to call the clinic for an emergency appointment as soon as possible. Participants are also advised not to brush their teeth 2 hours before their appointments.

